## Intervention

Patients will be given 24 times of treatments during 8 consecutive weeks, with each treatment lasting 30 min and 3 times of treatments per week (once every 2 days at an ideal condition). All the acupuncture therapists in this study have obtained the certificate of licensed practicing physician and have more than 5 years of experience in acupuncture operation. In order to improve the consistency of treatment in each center, the acupuncture therapists will receive a standard training before the treatment.

### Electroacupuncture group

Patients will be placed in a prone position, and local skin is routinely disinfected. The bilateral Zhongliao (BL33) and bilateral Xialiao (BL34) are selected. BL34 is located in the sacral region and faces the fourth posterior sacral foramina. For BL34, a 0.35 × 0.75-mm needle (Jiajian Medical Equipment Co., Ltd.) is vertically inserted into the fourth posterior sacral foramina. BL33 is located in the sacral region and faces the third posterior sacral foramina. For BL33, a 0.35 × 0.75-mm needle (Jiajian Medical Equipment Co., Ltd., Wuxi, China) is inserted into the third posterior sacral foramina and is at an angle of 70° to the coronal plane of the human body. After inserting, the needle is gently lifted, inserted, twirled, and rotated to achieve a Deqi sensation. After achieving the Deqi sensation, even a reinforcing-reducing method is conducted. The electroacupuncture (HM6805-II, Hengming Medical Company, Chengdu, China) is given in bilateral BL33 and BL34, with a dilatational wave, a frequency of 2/15 Hz, and a stimulation intensity of 1-5 mA, based on the patient’s tolerance level. The needle is left in the patient’s body for 30 min, and patients are not needled during this process.

### Sham electroacupuncture group

The bilateral sham BL33 (opening 20 mm outward at actual BL33) and bilateral sham BL34 (opening 20 mm outward at actual BL34) are selected, with shallow needling (0.35 mm × 25 mm, Jiajian Medical Equipment Co., Ltd., Wuxi, China) of 3–5 mm. The electrode placement and parameter settings of the electroacupuncture are the same as those of the electroacupuncture group, but the electricity is not turned on. After needling, there is no operation to achieve the Deqi sensation.

### Adverse event

The adverse reactions such as needle fainting, needle sticking, needle bending, and needle breaking during the electroacupuncture treatment, as well as adverse events such as empyrosis and getting blisters during the moxibustion, should be recorded. All adverse events should be treated appropriately based on the patient’s condition until the condition is stabilized. The adverse events can be processed by one or more of the following: taking no measures (mainly observation); adjusting electroacupuncture treatment measures such as reducing treatment frequency, reducing stimulation, and temporarily or permanently discontinuing electroacupuncture treatment; and providing non-drug therapies.

### Data collection and management

A case report form (CRF) will be used to collect study-related data. The CRF must be completed for every subject by the researcher. The completed CRF will be reviewed by clinical researchers and supervisors, and then be handed over to the data administrators. Data administrators will develop the data management system according to the CRF. To ensure the accuracy of data, two data administrators will independently enter and proofread the data. For queries in the CRF, data administrators will issue an inquiry to the researchers, and correct, confirm, and enter the data based on the researchers’ answer. After confirming the accuracy of all data, the database will be locked by the main researcher, sponsor, and statistical analyst. The locked data cannot be modified.

## Outcome measurement

### Primary outcome

#### Clinical treatment efficacy

Referring to the Guiding rules of clinical research of new Chinese medicine [14], the VAS score will be used to evaluate efficacy. VAS scores at baseline, 4 weeks and 8 weeks of treatment, and 1, 3, and 6 months of follow-up will be recorded, and clinical treatment efficacy is evaluated using the efficacy index. Efficacy index is calculated as [(pre-treatment VAS score − post-treatment VAS score) ÷ pre-treatment VAS score] × 100%. Curing is defined as the pain symptom completely disappears, and the VAS score reduction rate is ≥ 95%. Apparent effect is defined as the pain symptom broadly disappears, with occasional discomfort, and the VAS score reduction rate is ≥ 70% and < 95%. General effect is defined as the pain symptom is improved, with the non-ignorable discomfort during onset which does not affect life and work, and the VAS score reduction rate is ≥ 30% and < 70%. No effect is defined that the pain symptoms are not apparently improved, with the pain affecting life and work during onset, and the VAS score reduction rate is < 30%.

### Secondary outcomes

#### Pain days per month

The number of pain days per month will be evaluated based on 30 days of pain logs recorded before the baseline period, 4 weeks and 8 weeks of treatment, and 1, 3, and 6 months of follow-up. The pain logs will not be obtained by the therapists.

#### Quality of life

The quality of life will be assessed at the baseline period, 4 weeks and 8 weeks of treatment, and 1, 3, and 6 months of follow-up using a 36-Item Short Form Health Survey questionnaire (SF-36) [15]. SF-36 assesses the quality of life of the subjects based on 8 aspects: physical activities, physiological function, bodily pain, health perceptions, vitality (energy and fatigue), social activities, emotional function, and mental health [15]. The higher score in each aspect indicates the better the quality of life in this aspect [15].

#### Psychological state assessment

Psychological state will be evaluated using a Self-rating Anxiety Scale (SAS) and Self-rating Depression Scale (SDS) [16, 17]. Psychological state will be evaluated at the baseline period, 8 weeks of treatment, and 3 and 6 months of follow-up.

#### Anorectal manometry

Anorectal manometry will be performed to assess the anorectal function (anal sphincter function, rectal sensory function, and anorectal reflex) using the high-resolution anorectal manometry instrument. Outcome measures (1) anal sphincter function: anal resting pressure, maximum anal systolic pressure, rectal defecation pressure, and high-pressure zone; (2) rectal sensory function: initial threshold, defecation sensation threshold, and maximum tolerance; (3) anorectal reflex: defecation relaxation reflex, anorectal contraction reflex, and anorectal inhibition reflex. Anorectal manometry will be evaluated at the baseline period, 8 weeks of treatment, and 6 months of follow-up.

#### Pelvic floor surface electromyography

Pelvic floor electromyography will be performed to assess the pelvic floor muscle function by using a pelvic floor biofeedback therapeutic instrument with the Glazer Protocol. The process and detection indicators of Glazer Protocol are shown as the following: (1) pre-baseline: resting for 1 min, detecting amplitude and coefficient of variation (coefficient of variation = standard deviation/mean, the same below); (2) rapid contractions: conducting five rapid contractions with a 10-s rest between each contraction, detecting contraction response time and maximum contraction amplitude; (3) continuous contractions: conducting five contractions with resting for 10 s and continue to contract for 10 s, detecting the contraction amplitude, coefficient of variation, and median frequency; (4) endurance contraction: contracting continuously for 1 min, detecting amplitude, coefficient of variation, and median frequency; (5) post-baseline: resting for another 1 min, detecting amplitude and coefficient of variation. Pelvic floor electromyography will be evaluated at the baseline period, 8 weeks of treatment, and 6 months of follow-up.

#### Patient satisfaction

Patient satisfaction will be evaluated at the 6 months of follow-up using a 5-point Likert scale [18]. The scores range from 1 to 5 (1 = highly not satisfied, 2 = not satisfied, 3 = neutral, 4 = satisfied, and 5 = highly satisfied) [18].

#### Quality control

To ensure the quality of the study, acupuncturists, research assistants, and statisticians must receive unified training. A multi-center experimental coordination committee will be established to be responsible for the implementation of the entire study and resolving issues related to the study. Experienced personnels will serve as inspectors to guarantee the rights and interests of the subjects, confirm accuracy and completeness of the data, ensure the compliance of study to approved protocols and relevant regulations, and monitor the center regularly.

#### Sample size calculation

The sample size is calculated based on the previous study [19]. This study assumes a 70% effective rate in the electroacupuncture group and a 40% effective rate in the sham electroacupuncture group. *α* is taken as 0.05, and 1- *β* (power) is taken as 0.9. PASS 11.0 software (NCSS, LLC. Kaysville, Utah) is used to calculate the sample size, and 57 subjects will be required for each group. Considering a 15% dropout rate, 67 subjects are required for each group, and a total of 134 subjects are required. Due to the sample size jointly responsible by 4 centers and block randomization, each center will provide 34 subjects, and a total of 136 subjects are required.

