## Methods

### Study design

This is a multicenter, paralleled, randomized, controlled trial. The eligible patients will be randomly divided into the treatment group (electroacupuncture group) and control group (sham electroacupuncture group) at a 1:1 ratio. This study will last for 34 weeks, including 2 weeks before randomization (baseline), 8 weeks of treatment, and 24 weeks of follow-up. Follow-up will be conducted at baseline, 4 weeks of treatment, 8 weeks of treatment, and 1 month (12 weeks), 3 months (20 weeks), and 6 months (32 weeks) after the treatments. This study protocol conforms to the Consolidated Standards of Reporting Trials (CONSORT) [12] and Standards for Reporting Interventions in Clinical Trials for Acupuncture (STRICTA) [13]. This study followed the Declaration of Helsinki and has been approved by the Institutional Review Board of Nanjing Hospital of Chinese Medicine Affiliated to Nanjing University of Chinese Medicine, Longhua Hospital of Shanghai University of Traditional Chinese Medicine, Yinchuan Traditional Chinese Medicine Hospital, and Suzhou Hospital of Traditional Chinese Medicine Affiliated to Nanjing University of Chinese Medicine, approval no. KY2023012. Written consent form will be obtained from all patients. This study has been registered in the Chinese Clinical Trial Registry (registration no. ChiCTR2300069757) on March 24, 2023. The details of study design are demonstrated in Fig. 1, and the trial schedule is presented in the Supplementary information Table 1.

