### Randomization and blinding

The stratified block randomization will be taken in this study. Randomization will be stratified according to the center, and the block size is 4. Randomization is generated by SAS software (SAS Institute Inc., Cary, NC, USA), and allocation will be hidden through opaque sealed envelopes. The treatment allocation corresponding to serial no. 001–136 is listed (random coding table), and the serial number is corresponded to the number of subjects. A designated person will keep the random coding table. After subjects are selected, researchers will inform the random coding table keeper of the corresponding number of the subject. The keeper will give instructions to the subject to enter which group according to a random coding table. The researchers will record the instructions and comply with the corresponding allocation according to the instructions.

Due to the particularity of acupuncture operation, it is difficult to make operators and patients be blind. Therefore, outcome assessors and statisticians will be blind to reduce the risk of bias.

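### A fixed, disclosed block of 4 within each centre would let site staff who track allocations deduce about 31% of assignments; the centre size of 34 does not fit that block either

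*Protocol article*

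**What the plan says.** Under Randomization and blinding, the protocol article fixes the scheme: "Randomization will be stratified according to the center, and the block size is 4". On concealment it says that "allocation will be hidden through opaque sealed envelopes", and it also describes a keeper who holds the coding table for numbers 001 to 136 and gives the group once a subject has been selected and the number reported. Then: "The researchers will record the instructions and comply with the corresponding allocation according to the instructions". The same section concedes that "it is difficult to make operators and patients be blind" and for that reason has "outcome assessors and statisticians will be blind to reduce the risk of bias".

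Under Study design, the ratio is 1:1. Under Sample size calculation, 57 per group becomes 67 after 15% dropout, or 134 in all. The last step to 136 is explained as follows: "Due to the sample size jointly responsible by 4 centers and block randomization, each center will provide 34 subjects".

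**The concern.** There are two issues of unequal weight.

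**Predictability.** Blocking runs separately in each centre, the block is small, its size never varies and it is disclosed. Treatment is visible to operators and patients, and researchers write down each assignment, so a centre's past sequence can be known locally. In a block of two and two, the last assignment always follows from the first three, and sometimes the third follows from the first two. Someone who can foresee the next assignment can bring a patient forward, delay one or decline to enrol one. That is selection bias at entry, and it acts before any assessor sees the patient. Envelopes hide the next entry but do not stop deduction from the entries already opened.

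**Centre size.** Block randomisation is given as a reason for 34 per centre, yet 34 is not a multiple of 4. The stated rationale does not fit the stratum in which the blocks operate.

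**Working it through.** **Inputs** (protocol article). Block size 4, stratified by centre; 4 centres of 34; total 136; ratio 1:1; effective rates 70% and 40%; alpha 0.05; power 0.90; dropout 15%.

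**The plan's own figures.** The two-sided, pooled, uncorrected two-proportion formula gives 56 per group against 57 stated, which is close enough to count as reproduced. 57/0.85 = 67.06, stated as 67; 2 × 67 = 134; 134/4 = 33.5, rounded up to 34; 4 × 34 = 136. The sample size is not in dispute.

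**Divisibility.** 136/4 = 34 blocks exactly, but 34/4 = 8.5. Each centre has 8 full blocks and 2 places over, and 34 blocks cannot be shared equally among 4 centres.

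**Certain assignments with a known block of 4.** There are 6 equally likely orders of AABB.
- The fourth place is always determined: 1 per block.
- The third place is determined when the first two agree (AA or BB): 2/6 = 1/3.
- Expected per full block: 1 + 1/3 = 4/3, that is 33.3% of places.
- The two places of a cut ninth block add none.
- Per centre: 8 × 4/3 = 10.7 of 34 = 31.4%. Each full block gives 1 or 2, so the range is 8 to 16 of 34 (23.5% to 47.1%).
- Trial: 4 × 10.67 = 42.7, about 43 of 136.

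**Best-guess accuracy** (always guess the arm with more places left in the block). The chances of being right at places 1 to 4 are 1/2, 2/3, 2/3 and 1, a sum of 2.833 per full block. The two spare places give 1/2 + 2/3 = 1.167. Per centre: (8 × 2.833 + 1.167)/34 = 70.1%, against 50% by chance.

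**Balance, assuming that each centre's ninth block is a 2:2 block stopped after two places.**
- The two places split 1:1 with probability 4/6, and 2:0 or 0:2 with probability 1/6 each. So a centre ends 18:16 or 16:18 with probability 1/3.
- All four centres at 17:17: (2/3)^4 = 0.198.
- Overall 68:68: (2/3)^4 + 12 × (1/6)^2 × (2/3)^2 + 6 × (1/6)^4 = 0.198 + 0.148 + 0.005 = 0.350.
- Worst case 72:64, with probability 2 × (1/6)^4 = 0.0015.

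**Power after 15% dropout, at 70% against 40%.** 91.1% at 68:68 and 91.0% at 64:72.

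**Mixed blocks.** 4 × 4 + 3 × 6 = 16 + 18 = 34, split 17:17; four centres give 136. By simulation, for an observer who knows the composition but not the order of the blocks, certain calls are about 10% and best-guess accuracy is 69.5%.

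**The case against.** **On predictability.** The 31% applies only to someone who knows the block size and has followed every earlier assignment at that centre. The size is printed in a journal article; what the site documents told recruiters is not shown. The text does not say that the person who selects a patient is the person who records the group, and the keeper releases the group only after selection. All of this stands. The exposure is possible, not shown to have happened, and a reader who inferred that recruitment was or will be manipulated would go beyond the document. Releasing the group after selection does not remove the exposure, because the deduction is made from past assignments before the next patient is put forward.

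**On balance.** A reader might infer that the design breaks a promise of equal arms in each centre. It does not: no section promises 17:17 per centre, and a 1:1 ratio is compatible with an incomplete last block. Incomplete last blocks also arise whenever a centre stops off target. The imbalance figures assume a truncated ninth block, and the document does not say how the last two places are filled; a final block of 2 would give exactly 17:17. The planned Cochran-Mantel-Haenszel test for the multicentre analysis, if stratified by centre, accommodates small imbalances. This stands too, so the centre-size point is a flaw in the stated rationale with little consequence.

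**On the remedy.** Mixed blocks hardly change average guessing accuracy (70.1% against 69.5%). That is correct. What they cut is the share of assignments known for certain.

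**Conclusion.** The concern holds in a limited form. The main point is the fixed, disclosed block of 4 within centre in a trial whose operators and patients are unblinded: on average 31% of assignments, about 43 of 136, could be deduced with certainty. This rests on two conditions, that site staff know the block size and that they track their centre's earlier assignments. The published scheme makes both possible and establishes neither. Calling the trial simply open would also be too broad, since assessors and statisticians are blinded, although their blinding does not act at enrolment.

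The secondary point is that block randomisation justifies the total of 136 but not 34 per centre. Under the truncated-block assumption the cost is an imbalance of at most 2 in a centre and 8 overall, with power changing by about 0.1 percentage point. Alone, it would call only for a wording correction. Because the rule is stated and cheap to change, the scheme should be revised.

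**What to change.** Within each centre, use four blocks of 4 and three blocks of 6 in random order. This gives 34 exactly, 17:17 in each centre, and leaves the total at 136. Keep the block sizes out of any document that the sites see. Reword the sample size section so that the reason given for 34 agrees with the scheme.

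If blocks of 4 are kept, set centre targets that are multiples of 4, such as 36, 36, 32 and 32, which also total 136. That repairs only the arithmetic: with full blocks throughout, the certain share is 33.3%. Equal centres in multiples of 4 that reach at least 134 would need 4 × 36 = 144.

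It would also help to say how the envelopes and the keeper's table work together and at what moment the group is released, but this is clarification only.

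The cost is a new randomisation list, or a new list for the remaining places if recruitment has begun, and a paragraph of text. Certain calls fall from about 31% to about 10% even if the block composition becomes known. Guessing on the balance so far would still succeed about 70% of the time, so the change lessens the risk without removing it.

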### Statistical analysis

The continuous data in normal distribution will be expressed as mean ± standard deviation (mean ± SD), and differences between two groups are compared using *t* test, paired *t* test, or analysis of variance (ANOVA). The continuous data in skewed distribution will be expressed as medians and interquartile ranges (IQRs), and differences between the two groups are compared using a rank-sum test. The categorical data will be expressed as number (*n*) and percentage (%), and differences between the two groups are compared using the *χ*^2^ test or Fisher’s exact test. For comprehensive efficacy analysis of multi-centers, categorical data will be compared using the Cochran-Mantel-Haenszel *χ*^2^ test, and continuous data will be compared using analysis of covariance. SAS 9.4 (SAS Institute Inc., Cary, NC, USA) will be used for statistical analysis, and *P* < 0.05 is regarded as the statistical significance.

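### The paired t test is listed as a between-group comparison of independent arms, and unadjusted tests and ANCOVA both cover the same continuous outcomes with neither named as the main analysis

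*Protocol article*

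**What the plan says.** All quotes are from the protocol article.

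- **Design** (Study design): "This is a multicenter, paralleled, randomized, controlled trial", with patients allocated to electroacupuncture or to the "control group (sham electroacupuncture group) at a 1:1 ratio".
- **Stratification** (Randomization and blinding): "Randomization will be stratified according to the center, and the block size is 4".
- **Normally distributed continuous data** (Statistical analysis): "differences between two groups are compared using *t* test, paired *t* test, or analysis of variance (ANOVA").
- **Skewed continuous data** (same section): "differences between the two groups are compared using a rank-sum test".
- **Multicentre efficacy analysis** (same section): "For comprehensive efficacy analysis of multi-centers, categorical data will be compared using the Cochran-Mantel-Haenszel" test, and "continuous data will be compared using analysis of covariance". No covariate is named, and nothing says how this analysis ranks against the tests listed before it.
- **Outcomes affected** (Secondary outcomes): pain days, SF-36, the anxiety and depression scales, manometry and electromyography all have a baseline value and at least two later ones. For SF-36, for example, "The quality of life will be assessed at the baseline period, 4 weeks and 8 weeks of treatment, and 1, 3, and 6 months".

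**The concern.** There are two problems, and both are in the text as printed.

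**A test that does not fit the comparison.** A paired t test needs natural pairs. In a parallel trial the only pairs are a patient's own earlier and later values, so the test asks whether an arm changed from baseline. Pain and quality of life can improve under sham as well; the sample size calculation itself assumes that 40% of sham patients respond. If one arm's change is significant and the other's is not, it is easy to report that as a treatment effect, which it is not.

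**Two analyses, no order.** All four centres contribute to every outcome, so the general rule (t test or ANOVA, or rank-sum if skewed) and the ANCOVA rule cover the same data. They can disagree, and the article does not say which result counts. That leaves room to choose after seeing the results. It also risks leading with the analysis that ignores baseline and the randomisation stratum.

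**Working it through.** **1. The plan's own figure.** The only stated sample size calculation is for the binary effective rate: 70% against 40%, α = 0.05, power 0.90, giving 57 per group. Two-sided with pooled variance, and mean proportion 0.55:

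n = [1.96·√(2·0.55·0.45) + 1.2816·√(0.70·0.30 + 0.40·0.60)]² / 0.30² = (1.379 + 0.860)² / 0.09 ≈ 55.7, so 56.

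This is within one patient of the stated 57. The calculation does not involve any continuous outcome, so nothing below changes it. I use 57 per arm as the evaluable number.

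**2. The paired test against the design.** Study design gives two independent arms at 1:1, with no matching across arms. Two uses of a paired t test are conceivable:

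- *Pairing patients across arms arbitrarily.* In simulation under no difference, the test keeps its size (4.8% at a nominal 5%). The pairing has no basis, but this is not where the harm lies.
- *Testing baseline against follow-up within each arm.* This is the natural use, and it does not compare arms. Suppose both arms have the same true change and each within-arm test has power π. The chance that exactly one arm is significant is 2π(1 − π), which reaches 50% at π = 0.5. Simulation with 57 per arm and 20,000 trials, with the true change assumed:

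| True change in both arms (SD of change) | Exactly one arm significant | Only one given arm significant (e.g. electroacupuncture) |
|---|---|---|
| 0.2 | 43% | 22% |
| 0.3 | 48% | 24% |
| 0.4 | 27% | 13% |

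There is no treatment difference in any row.

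**3. How many between-arm analyses per outcome.** The t test and rank-sum test are alternatives by distribution. ANOVA with two groups is the equal-variance t test (F = t²). The paired test asks a different question. That leaves two: one unadjusted test and ANCOVA. For SF-36, 8 domains × 5 post-baseline visits = 40 possible contrasts, each with two permitted P values if all are reported.

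**4. What is at stake in the order.** With the same variance σ² in both arms and correlation r between baseline and follow-up, the variance of the arm difference is about 2σ²/n unadjusted and 2σ²(1 − r²)/n with baseline as covariate. The unadjusted test would need 1/(1 − r²) times as many patients for the same precision. For power I assume a standardised difference of 0.5 and use power = Φ(0.5·√(57/2)/√(1 − r²) − 1.96). Unadjusted, this is Φ(2.669 − 1.96) = 0.76.

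| r (assumed) | Variance ratio 1 − r² | Equivalent extra patients | Power, baseline-adjusted |
|---|---|---|---|
| 0.3 | 0.91 | 10% | 0.80 |
| 0.5 | 0.75 | 33% | 0.87 |
| 0.7 | 0.51 | 96% | 0.96 |

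The article gives neither r nor an effect size for any continuous outcome. These figures apply only if the unadjusted test leads, or if the ANCOVA omits baseline. Any gain from centre depends on between-centre variation, which is also not given.

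**The case against.** The strongest reply is that the adjusted analysis is already planned. ANCOVA implies at least one covariate, it sits in the multicentre efficacy analysis, and covariate lists normally belong in the SAP, which is not shown. The paired test is probably loose wording for before-and-after change within an arm, and choosing between t and rank-sum by distribution is conventional. Much of this stands, and it rules out several stronger readings that a reader might infer:

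- *Baseline and centre are left unused.* Not supported. The planned ANCOVA contradicts it; only the covariates and the ranking are open.
- *Tests will be run visit by visit and patients with a missing visit dropped.* The article says neither. Under Elimination criteria it commits to intention-to-treat analysis of eliminated and lost patients, and the detail may sit in the SAP.
- *VAS will never be analysed on its own scale.* Not established. The rules for continuous data do not exclude it. Adding continuous VAS as a listed outcome would be a design suggestion, not a correction.
- *The precision gains are owed to the fix in any case.* They are not; they hold only under the condition given with the table.
- *A repeated-measures model is required.* ANCOVA at a named visit is also sound, so this is a preference.

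Two things remain. As written, the sentence puts the paired test among comparisons of the two groups, which is wrong whatever the intent. The article also states two between-arm rules for the same outcomes and does not rank them. That is an overlap in the stated text, not a detail left out.

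**Conclusion.** The point holds in this limited form and should be corrected. The paired t test is an outright error as a between-group comparison; that conclusion rests only on the parallel design. The overlap between the unadjusted tests and ANCOVA is unresolved, and it allows two P values per continuous outcome.

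Reading within-arm tests as a comparison of arms could mislead in roughly a quarter to a half of trials with no treatment difference, under the assumed changes. The cost of letting the unadjusted tests lead ranges from small (variance ratio 0.91) to large (0.51), depending on a correlation that the article does not give.

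The reach is mainly the secondary outcomes. The primary outcome is a categorised VAS reduction, which falls under the χ² and Cochran-Mantel-Haenszel wording, and the sample size rests on a binary rate. Neither changes.

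**What to change.** In the Statistical analysis section, and in the SAP if there is one:

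1. Remove the paired t test from the between-arm comparisons, or keep it under a separate label as descriptive change within an arm, with a statement that no conclusion about treatment will be drawn from it.
2. Name one main analysis for continuous outcomes: ANCOVA with arm, baseline value and centre, or a repeated-measures model with the same terms plus visit and arm-by-visit. Where there is no baseline, as for patient satisfaction if it is analysed as continuous, adjust for centre alone.
3. Report the adjusted difference with its 95% CI at one named visit. Week 8 and 6 months are the two post-baseline visits at which all the repeatedly measured continuous secondary outcomes are scheduled.
4. Keep the unadjusted t test and the rank-sum test as sensitivity analyses.

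The cost is a few sentences and a little programming. Baseline values and centre are already recorded, so no new data or patients are needed. The change should be dated before the treatment codes are opened to the statisticians.
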